**Table 4**

| Parameters for Attenuation Scan | Description                                         | Note                                                                                 |
|---------------------------------|-----------------------------------------------------|--------------------------------------------------------------------------------------|
| Energy window                   | 20% symmetric, peaked on 122 keV (110-134 keV)      |                                                                                      |
| Scan Speed                      | 20 cm/min                                           | Note faster than patient scans                                                       |
| Matrix                          | 256 x 1024 minimum                                  |                                                                                      |
| Attenuation Correction          | NA                                                  |                                                                                      |
| Scatter Correction              | NA                                                  |                                                                                      |
| Collimator                      | Parallel hole, high energy                          | Ultra high energy collimators for 511 keV SPECT will not be used for this protocol   |
| Views                           | Anterior (place Co-57 source on posterior detector) | Acquire patient images with ant detector – place Co-57 sheet source on post detector |
| Data to be recorded             |                                                     | Data worksheet will be provided                                                      |

**Day 0: 15-35 min post injection**

1. Patients should not void their bladder between injection and imaging time, because all activity must be accounted for in the immediate post injection images.
2. The same camera that was used for the attenuation scan must be used for all patient images.
3. Attempt to position the patient as consistently as possible for each imaging session: flatly supine, arms to the side, head and neck straight forward.
4. At the foot of the patient, visible to the camera but not touching the patient, place the known activity reference source of I-131. This source will be placed in the field of view for calibration purposes at each imaging session.
5. Acquire anterior/posterior whole body image of patient 15 minutes post injection, using parameters described in the table below.
6. Record any unusual image findings on the worksheet provided (i.e. hot injection site, image artifact, etc.)

**Table 5**

| Parameters for Patient Imaging | Description                             | Note                                                                                            |
|---------------------------------------|------------------------------------------------|--------------------------------------------------------------------------------------------------------|
| I-131 calibration source              | Place at foot of patient                       | Tape vial to bed to eliminate motion                                                                   |
| Energy window                         | 20% symmetric, peaked on 364 keV (328-400 keV) |                                                                                                        |
| Scatter correction windows            | 20% symmetric, peaked on 298 keV and 436 keV   | Triple Energy Window (TEW) method; applied during acquisition                                          |
| Scan Speed                            | 10 cm/min                                      | Record scan speed in case report form; use consistent scan speed for all imaging sessions on Days 1-4. |
| Matrix                                | 256 x 1024                                     |                                                                                                        |
| Attenuation Correction                | NA                                             | Will be applied post-processing at central lab                                                         |
| Collimator                            | Parallel hole, high energy                     | Ultra high energy collimators for 511 keV SPECT will not be used for this protocol                     |
| Views                                 | Complete anterior and posterior                | Include extremities; do not overlap arms with torso; scans to be centered on midline of body           |
| Data to be recorded                   |                                                | Data worksheet will be provided                                                                        |

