## 7. STUDY DRUG ADMINISTRATION

### 7.1 DESCRIPTION OF STUDY DRUG

I-131-CLR1404 is supplied as a ready-for-use radiopharmaceutical for intravenous dosing that is provided as a clear, faint yellow to yellow, sterile solution consisting of I-131-CLR1404 (18-(*p*-[I]iodophenyl)octadecyl phosphocholine) and CLR1401 (18-(*para*-iodophenyl)octadecyl phosphocholine) in sodium chloride injection USP, ethanol USP/NF, polysorbate 20 NF, and sodium ascorbate USP. The study drug is packaged in a single-use glass vial and must be withdrawn through a 25 mm, 0.22 or 0.45 micron sterile filter prior to administration. **The appropriate volume of study drug sufficient to give a measured 10 mCi dose must then be diluted to 10 ml with normal saline solution (normal saline for injection) and thoroughly mixed prior to administration via slow IV infusion.**

I-131-CLR1404 is radioactive and should only be prepared, assayed, and administered by personnel who are licensed and trained to handle radioactive materials. Proper radiation shielding should be used during storage, preparation, assay, and administration of I-131-CLR1404. The study drug will arrive from Collectar in a lead shipping container, and should remain in the lead shipping container for storage, out of direct sunlight and at room temperature.

The physical half-life of iodine-131 is approximately 8.02 days. Iodine-131 decays with beta emissions of 334 keV (7.3%) and 606 keV (89.9%), and gamma emissions of 284.3 keV and 364.5 keV. The therapeutic radiation effects are primarily from beta emissions, while gamma emissions are useful for imaging.

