## **7.7 STUDY ENDPOINTS**

### **7.7.1 Primary Endpoints**

The primary endpoints are:

- Whole body and organ radiation dosimetry of I-131-CLR1404
- Determination of the millicurie (mCi) dose which is expected to deliver 35-40 centigray (cGy) of radiation to bone marrow, which will serve as the starting dose for a subsequent MTD study

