#### 8.2.3.14 *Whole Body Imaging*

Planar whole body nuclear medicine scans will be obtained of the patient, from the anterior and posterior projection, at the following times post injection: 15 – 35 minutes, 4-6 hours, 18-24 hours,  $48 \pm 6$  hours,  $72 \pm 6$  hours,  $144 \pm 6$  hours, and  $14 \pm 1$  Days. These images will be acquired with a high energy parallel hole collimator, on a triple energy window with a 20% symmetric peak, at a minimum of 256 x 1024 matrix, and for a speed of no faster than 10 cm/min. With the exception of the scan acquired 15 minutes post injection, the patient should void their bladder prior to each imaging session. For details regarding patient positioning, camera quality control, and image acquisition, refer to **Appendix D: Whole Body Scanning and Dosimetry** as well as the Nuclear Medicine and Radiopharmacy Manual.

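### In Table 5 the upper scatter window overlaps the photopeak and the lower one contains the 284.3 keV line, so scatter correction subtracts some true I-131 counts

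*Protocol*

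**What the plan says.** Appendix D, Table 5 gives the photopeak window as "20% symmetric, peaked on 364 keV (328-400 keV" and the scatter windows as "20% symmetric, peaked on 298 keV and 436 keV", without keV limits for the latter. It describes the correction as "Triple Energy Window (TEW) method; applied during acquisition". Attenuation correction, by contrast, is left to post-processing at the central laboratory.

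Section 8.2.3.14 describes acquisition "on a triple energy window with a 20% symmetric peak" and gives no other scatter limits. Section 7.1 lists for I-131 "gamma emissions of 284.3 keV and 364.5 keV". Appendix D places a known I-131 source in the field of view at every session. The images supply the primary endpoint, "Whole body and organ radiation dosimetry of I-131-CLR1404" (section 7.7.1).

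The scan-speed note in Table 5 reads "use consistent scan speed for all imaging sessions on Days 1-4". Whole body imaging is scheduled on Days 0, 1, 2, 3, 6 and 14.

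**The concern.** Triple-energy-window (TEW) correction treats every count in the two side windows as evidence of scatter and subtracts a width-weighted estimate from the photopeak. That works only if the side windows hold few unscattered photons. Here one of them shares energies with the photopeak, and the other includes an emission line of the same isotope. Some true counts would be removed from the images that feed the organ and marrow dosimetry.

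The scan-speed note has a similar weakness. It names a day with no scan (Day 4). It omits Day 0, when all injected activity must be accounted for, and the Day 6 and Day 14 scans, which define the tail of the time-activity curve.

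**Working it through.** **Meaning of 20% symmetric.** The rule is centre × 0.90 to centre × 1.10. The protocol's own printed ranges confirm it:
- Table 5, 364 keV: 327.6-400.4, printed as 328-400.
- Table 4, "20% symmetric, peaked on 122 keV (110-134 keV": 109.8-134.2, which rounds to the printed figures.

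**Scatter windows under the same rule.**
- Lower, 298 keV: 268.2-327.8 keV. This meets the photopeak to within 0.2 keV, which is rounding. Since 268.2 < 284.3 < 327.8, it contains the 284.3 keV line.
- Upper, 436 keV: 392.4-479.6 keV. The overlap is 400.4 − 392.4 = 8.0 keV (7.6 keV against the printed 400), and 8.0/72.8 = 11% of the photopeak width. It does not contain 284.3 keV.

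**Alternative reading.** If both scatter windows had the photopeak's printed width of 72 keV, they would be 262-334 and 400-472 keV. The upper one then adjoins, but the lower one overlaps by 334 − 328 = 6 keV and still contains 284.3 keV. The two centres follow different rules: 328/1.1 = 298.2 fits a 20% window that adjoins, while 400 + 36 = 436 fits a 72 keV window that adjoins. Neither reading clears both windows.

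**Can a 20% lower window be saved?** A window that ends at 327.6 and excludes 284.3 must be narrower than 327.6 − 284.3 = 43.3 keV, about 14% of its own centre, even before energy blur. A 20% window cannot both adjoin the photopeak and exclude the line.

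**Size, on assumed inputs.** The protocol names TEW but prints no formula. The usual form is

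S = (C_low/W_low + C_up/W_up) × W_peak/2,

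with W_low = 59.6, W_up = 87.2 and W_peak = 72.8 keV. Each true count in the lower window then costs 72.8/(2 × 59.6) = 0.61 of a count, and each in the upper window 72.8/(2 × 87.2) = 0.42. The model is a scatter-free source with Gaussian peaks at 364.5 and 284.3 keV and a peak width that grows with the square root of energy. Resolution and the detected 284/364 ratio are assumptions, not protocol figures. Unscattered counts removed, as a share of photopeak counts:

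| FWHM | ratio 0 | ratio 0.05 | ratio 0.10 |
|---|---|---|---|
| 8% | 0.6% | 3.4% | 6.3% |
| 10% | 2.1% | 4.8% | 7.5% |
| 12% | 4.5% | 7.1% | 9.8% |

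In the middle cell, 2.7% comes from the 284.3 keV line, 1.5% from the upper window (1.1% from the overlap strip alone) and 0.6% from the low tail of the 364.5 keV peak. Over the whole grid the overlap strip accounts for 0.4-1.8% and the line for 0-5.7%. None of this allows for the reference source.

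**Scan speed.** Days 1-4 covers three of the six imaging days (1, 2 and 3). Table 5 states 10 cm/min, while section 8.2.3.14 sets 10 cm/min only as a maximum.

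**The case against.** The strongest reply is calibration. The known I-131 source is imaged through the same windows at each session, and the cameras are calibrated against an I-131 standard before the study. A loss that is proportional in patient and source cancels in the ratio. The overlap strip removes much the same fraction of unscattered 364 keV counts from both, so that part should largely cancel. This stands, and it means the count losses above are not dose errors. Cancellation is not assured for the 284.3 keV part, because the source lies outside the patient and tissue attenuates the two lines differently.

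A reader might go further and infer that activity is understated, the marrow coefficient too low and the next study's mCi dose too high. The documents do not support that. Tissue attenuates the lower-energy line more, so the patient may lose a smaller fraction than the source, and scaling to the source would then overstate unscattered activity. Take 10% FWHM, ratios of 0.05-0.10, an attenuation difference of 0.005-0.015 per cm and depths of 5-15 cm, all assumed. The net residual is then about +0.1% to +1.2%, small and of the opposite sign. For the same reason the gross loss should not be set against the width of the 35-40 cGy target (37.5 ± 2.5, or ±6.7%). Section 11.4 also brings blood and urine data into the dosimetry.

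It is equally tempting to call the subtraction irreversible. Appendix D has raw nuclear medicine data sent to the core laboratory, and site manuals that are not shown may say more. What stands is that the protocol does not require the three window counts to be kept separately.

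On scan speed, each patient imaging session in Appendix D invokes Table 5, which states 10 cm/min, and the speed is recorded. The note is therefore probably a slip and does not exempt the other days. Even so, section 8.2.3.14 would allow a slower late scan, and sites may want one: by Day 14 physical decay alone leaves 0.5^(14/8.02) = 30% of the activity.

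**Conclusion.** The specification error holds on the protocol's own figures. The upper scatter window overlaps the photopeak by about 8 keV, and the lower window contains the 284.3 keV line. It would be wrong to read both faults into both windows. That some unscattered I-131 counts are subtracted as scatter follows without any outside figure.

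The amount does not. The range of 0.6-9.8% of photopeak counts rests on 8-12% FWHM, a detected line ratio of 0-0.10, no scatter or attenuation, and no cancellation by the reference source. Neither size nor direction is established for the marrow dose or the next study's mCi dose. The Days 1-4 note is a separate, smaller error in the same table. Both should be corrected because the images carry the primary endpoint and the change is cheap.

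**What to change.** In Table 5:

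1. Print keV limits for both scatter windows that do not overlap the photopeak. A 20% upper window that adjoins it is centred at 400.4/0.9 = 444.9, so near 445 keV rather than 436. In the model above at 10% FWHM, this lowers the upper-window part from 1.5% to 0.4%.
2. Choose lower-window limits that exclude 284.3 keV, or state how that line is corrected for.
3. Check the chosen limits against measured camera resolution at the I-131 camera qualification. Narrow windows against the peak are not a safe default. For example, 308-328 with 400-424 keV removes 8.9-10.2% at 12% FWHM, against 4.5-9.8% for Table 5. At 8-10% FWHM such windows do better once the 284.3 keV line contributes.
4. Keep the photopeak and two scatter-window counts separately, so that the central laboratory can apply or redo the correction.
5. Replace Days 1-4 with all imaging sessions (Days 0, 1, 2, 3, 6 and 14), and make section 8.2.3.14 agree with Table 5 on scan speed.

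The cost is a camera preset and table text, best settled before cameras are qualified, and possibly slightly noisier scatter estimates if the windows are narrower.

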**Day 0: 4-6 hours post injection**

1. Have the patient void their bladder prior to imaging.
2. Acquire whole body planar images with calibration source using the parameters listed in Table 5.

**Day 1: 18-24 hours post injection**

1. Have the patient void their bladder prior to imaging.
2. Acquire the whole body planar images with calibration source using the parameters listed in Table 5.

**Day 2: 48 hours  $\pm$  6 hours post injection**

1. Have the patient void their bladder prior to imaging.

2. Acquire the whole body planar images with calibration source using the parameters listed in Table 5.

**Day 3: 72 hours  $\pm$  6 hours post injection**

1. Have the patient void their bladder prior to imaging.
2. Acquire the whole body planar images with calibration source using the parameters listed in Table 5.

**Day 6: 144 hours  $\pm$  6 hours post injection**

1. Have the patient void their bladder prior to imaging.
2. Acquire the whole body planar images with calibration source using the parameters listed in Table 5.

**Day 14  $\pm$  1 Day**

1. Acquire the whole body planar images with calibration source using the parameters listed in Table 5.
2. Have the patient void their bladder prior to imaging.

**Optional SPECT Imaging**

At the Investigator's discretion, SPECT imaging may be performed between Days 3 and 14 to further characterize the patient's tumor(s).

**Data Analysis**

Dosimetry data analysis will be performed at a central laboratory. Instructions will be provided for preparing the nuclear medicine raw data and transmitting it to the core laboratory.

## APPENDIX E: GLOSSARY OF ABBREVIATIONS

|                  |                                           |
|------------------|-------------------------------------------|
| AE               | adverse event                             |
| ASCO             | American Society of Clinical Oncology     |
| AST              | aspartate aminotransferase                |
| AUC              | area under the concentration curve        |
| BP               | blood pressure                            |
| BSA              | body surface area                         |
| CBC              | complete blood count                      |
| cGy              | centiGray                                 |
| C max | maximum plasma concentration              |
| CRF              | case report form                          |
| CT               | Computed Tomography                       |
| CTC              | Common Toxicity Criteria                  |
| CV               | curriculum vitae                          |
| DBP              | diastolic blood pressure                  |
| DCF              | data clarification form                   |
| DHHS             | Department of Health and Human Services   |
| dL               | deciliter(s)                              |
| DLT              | dose-limiting toxicity                    |
| ECG              | electrocardiogram                         |
| ECOG             | Eastern Oncology Cooperative Group        |
| FDA              | Food and Drug Administration              |
| g                | gram(s)                                   |
| Gy               | gray                                      |
| HIV              | Human Immunodeficiency Virus              |
| I-131            | Iodine-131                                |
| ICF              | informed consent form                     |
| ICH              | International Conference on Harmonization |
| IND              | investigational new drug                  |
| INR              | International Normalized Ratio            |
| IRB              | Institutional Review Board                |
| IV               | intravenous                               |
| keV              | kiloelectron volts                        |
| kg               | kilogram(s)                               |
| LVEF             | Left Ventricular Ejection Fraction        |

---

|                               |                                            |
|-------------------------------|--------------------------------------------|
| mCi                           | millicurie(s)                              |
| mg                            | milligram(s)                               |
| mL                            | milliliter(s)                              |
| MTD                           | maximum tolerated dose                     |
| m                 | meters squared                             |
| NCI                           | National Cancer Institute                  |
| OLINDA                        | Organ Level INternal Dose Assessment       |
| PICC                          | peripherally inserted central catheter     |
| PK                            | pharmacokinetics                           |
| PLE                           | phospholipid ether analog                  |
| q.d                           | every day                                  |
| USP                           | U.S. Pharmacopeia                          |
| SAE                           | serious adverse event                      |
| S a O 2 | saturated oxygen                           |
| SBP                           | systolic blood pressure                    |
| SPECT                         | single photon emission computed tomography |
| SOPs                          | standard operating procedures              |
| t.i.d                         | three times a day                          |
| V d                | volume of distribution                     |
| WMA                           | World Medical Association                  |
